**LIST OF ABBREVIATIONS AND DEFINITIONS**

kDa – kilo Dalton - measurement of weight

CSF – Cerebrospinal fluid

AF – Antisecretory factor

ICP – Intracranial pressure

CT – Computerized tomography

GCS – Glasgow Coma Scale – a way of assessing comatose patients

1. **INTRODUCTION**
   1. **Background**

Brain edema arise in trauma and in conjunction with other pathologies in the brain such as infectious diseases, intracranial tumors and ischemic events, i.e. stroke.

Edema can form inside of the cells – intracellular or cytotoxic edema, and outside of the cells – extracellular, vasogenic edema.

The mechanisms underlying the formation of edema are not fully understood. In the injured brain, leakage over the blood brain-barrier arise, transporting fluid from the blood to the extracellular space. This process is disadvantageous because the influx of fluid leads to an increase in distance for diffusion of nutrients and oxygen. The edema increases the intracranial pressure, which leads to a systemic increase in blood pressure, that in turn causes more fluid to leak through the damaged blood brain-barrier. In addition to the physiological, flow-related changes that arise, the edema is also worsened by the inflammatory response to damage. In the injured brain, pro-inflammatory cytokines that can give rise to both intracellular and extracellular edema are released. Also other secondary events such as spreading depression and excitatory damage can worsen the insult.

Existing treatment can, at best, stop the development of edema, and marginally decrease an existing edema. Patients with manifest edema will receive neurointensive care with close monitoring of vital parameters. Patients with a manifest cerebral edema and a decreased level of consciousness are sedated and put on a ventilator. The sedation serves to diminish stress and to lower the basal metabolism of the brain. The lowered metabolism means that the patient´s systemic blood pressure can be kept lower than usual, which in turn means that less blood flows over the damaged blood brain-barrier per time unit, hopefully minimizing the development of further cerebral edema. Sedation and control of the brain´s perfusion pressure is the only available treatment to control and minimize cerebral edema today. There is no specific treatment against the immunological component of cerebral edema.

If the edema becomes expansive enough to give rise to a significant increase in intracranial pressure that may threaten the circulation to the brain surgery must be performed. The most common procedure is hemicraniectomy, which means that the surgeon removes as much as possible of the skull bone over one hemisphere, two hemispheres or bi-frontally. In the procedure, the dura is opened as well. A protective film is placed over the brain and the skin-flap is sutured back in place. After this procedure, the brain may swell out through the bone defects and the intracranial pressure usually normalizes. The procedure itself is risky, and re-operations due to hematoma, CSF-leakage and more are common. Furthermore, it is not known how the procedure itself affects the brain in terms of increased swelling, tearing of the brain etc.

Antisecretory factor (AF) is a 41 kDa protein that exists in most mammals. It was first discovered due to its ability to inhibit experimental diarrhea. AF has been shown to modulate the proliferation of memory/effector T-cells and is expressed by cells in the immune system. In animal experiments, antibodies directed towards AF have been shown to up regulate the pro-inflammatory cytokines IL6 and IL8 and to decrease the anti-inflammatory cytokine IL10. Endogenous AF secretion increases after exposure to bacterial toxins and an increase in AF secretion in combination with an immune reaction may be a part of normal defense against the secretory and inflammatory component in diarrhea. AF has also been shown to be effective against vertigo symptoms in Meniere’s disease, which is caused by an abnormal collection of lymph around the balance nerve. In a trauma model in rats, AF has been proven very efficient in reducing increased intracranial pressure to close to normal values.

The functional amino-terminal part of AF has been synthesized as a 16 amino-acid peptide – AF16. AF16 has been tested in animal experiments. In a herpes encephalitis model in rats, a majority of animals had severely increased intracranial pressure. After administration of AF16, all animals had reduced intracranial pressure. These findings suggest that AF may be involved in modulating the inflammatory processes that lead to cerebral edema and increased intracranial pressure.

AF is commercially available as Salovum®^®^ and is a product based on egg yolk powder B221^®^ as the source for AF. It is available in pharmacies without prescription. Salovum®^®^ is classified as a “medical food” by the European Union (see Appendix 1. Salovum®^®^ is currently registered in the Republic of South Africa.

- 1. **Study Rationale**

To this date, no efficient treatments exist against traumatic cerebral edema. AF has been shown to counteract edema caused by other pathologies in humans. Animal experiments have proven AF to reduce traumatic cerebral edema and reduce development of focal hemorrhagic contusions.

Since 1,5 years, AF has been given to adult patients with severe traumatic brain injury in the Department of Neurosurgery, Lund University Hospital, Sweden. Our preliminary findings suggest that in at least 3 out of 5 patients, AF has had an effect in reducing ICP and thereby avoiding decompressive hemicraniectomy. The study has been granted ethical permission (see Appendix 2). Salovum® has been a classified as a food supplement by the local ethics committee and the Swedish Pharmaceutical Agency (see Appendix 2)

Though, the number of patients with severe traumatic head injury in Sweden is decreasing and the need for a larger, randomized trial in a centre with large volumes of traumatic brain injury is needed

To evaluate if AF can be beneficial for patients in this group, we plan to perform a prospective, randomized double-blinded, placebo-controlled trial.

1. **STUDY OBJECTIVES**

The primary objective of this study is to evaluate the effect of the protein Antisecretory factor (AF), given as a dietary supplement to adult patients with severe traumatic brain injury. We will assess 30-day mortality, ICP, and treatment intensity level (TIL, see Appendix 3) for this purpose.

1. **STUDY PLAN AND PROCEDURES**
   1. **Study status**

After approval by the ethics committee, recruitment started in September 2017. Expected end date is June 2021. The trial was registered at [www.clinicaltrials.gov](http://www.clinicaltrials.gov) with NCT03339505 on September 17, 2017. The study is expected to be completed by June 2021.

- 1. **Study design**

The study is prospective, double-blinded, placebo-controlled, and interventional.

Primary outcome for this study will be 30-day mortality.

Secondary outcomes will be ICP and TIL (Treatment Intensity Level).

Patients that fit the inclusion criteria will be asked to participate via next of kin when admitted to the NICU at Tygerberg University Hospital. If consent is given, the patient will be screened for eligibility. After enrolment in the study, randomization will take place and the patient will be given either Salovum® or egg powder placebo, according to 1g/kg body weight/24 hours. The total dosage will be divided into 6 equal amounts and given to the patient orally via the nasogastric tubing every 4 hours for 5 consecutive days. Placebo group patients will receive supplement according to the same procedure.

ICP, mean arterial pressure (MAP), Treatment Intensity Level (TIL) will be registered for later analysis.

- 1. **Study duration**

The study is anticipated to run for a time period no longer than 4 years.

- 1. **Study funding/budget**

1100 000 Rands for covering costs for the trial will be provided from research funds at Lund University Hospital, Sweden.

- 1. **Study monitoring**

The study will be monitored by an external monitoring company. Monitoring will take place at regular intervals (2-4 times per year, depending on recruitment progression) Novotech (novotech-cro.com, [name]).

- 1. **Interim analysis**

An independent Data and Safety Monitoring Committee (DMC) will perform an unblinded interim analysis when 95 patients have been included. The interim analysis will be conducted by an unblinded statistician and reviewed by the DMC, based on clean data on the primary

and secondary outcome variables. The outcome of this interim analysis will result in one of three possible recommendations of the DMC to the Sponsor to do one of the following:

- Stop the study because of futility
- Continue and finalize the study as planned
- Continue the study as planned but increase the sample size to a specified number of patients
  1. **Study population**

The study population will be adult patients (18-65 years) that are treated in the NICU for severe traumatic brain injury. Recruitment will be via the patients´ next of kin, who will be asked about participation in the study. Recruitment will continue until 100 patients have been randomized into the 2 groups (active substance and placebo) of 50 patients each. If no next of kin can be found, the patient can be included in the study according to paragraph 30 Helsinki Declaration (see also 3.7.2).

- 1. **Inclusion criteria**

To be enrolled, the following criteria have to be fulfilled:

1. Adult of either gender between 18 and 65 years.
2. Non-penetrating, isolated severe traumatic brain injury
3. GCS >3 and GCS<9 on admission or within 48 hours after injury*
4. Admission to study hospital within 24 hours of injury*
5. No known history of allergy to egg-protein
6. Planned for intracranial pressure monitoring
7. Absence of bilaterally dilated pupils
8. CT scan with traumatic pathology that is more than an isolated epidural hematoma

*Within 24 hours of injury (for patients with GCS < 9 on admission) or

Within 24 hours of deterioration (among patients deteriorating to GCS < 9 within 48 hours of injury)

- 1. **Exclusion criteria**

Any of the following is regarded as a criterion for exclusion from the study:

1. No consent
2. Systolic blood pressure below 90 mm Hg post resuscitation
3. Non-fulfillment of inclusion criteria after screening and inclusion procedures.

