**8.2.3** **Non-maleficence**

The risk of harm to participants is estimated to be extremely low. The management of severe traumatic brain injury for all participants in the study conforms to the current protocols and practices at Tygerberg Hospital, and will be identical between the two groups. There will also be no deviation in the surgical and follow-up regimes of the patients involved. The only difference between the two groups will be that one group will receive Salovum® (e.g. antisecretory factor enriched egg yolk powder) as part of their daily dietary intake, and the other group will receive ordinary egg yolk powder. Both supplements are high in protein and contain only natural nutrients that will be part of the patients´ daily nutritional demand. Salovum® has been used for many years in high doses for patients with various diagnoses, and there is no known toxicity, neither has there been any signs of immune reactivity in the form of antibody production. Salovum® has been given to adult patients with severe traumatic head injury in the department of Neurosurgery, Lund University Hospital, Lund, Sweden, during a clinical trial since January 2014. Salovum® has been shown to have a very promising effect on lowering ICP and decreasing the need for re-operations in this trial without any signs of toxicity.

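### The interim analysis allows the DMC three recommendations, none of them to pause or stop for safety, and it takes place at 95 of the planned 100 patients

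*Protocol*

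**What the plan says.** The Interim analysis section of the protocol sets up the look: "An independent Data and Safety Monitoring Committee (DMC) will perform an unblinded interim analysis when 95 patients have been included". An unblinded statistician runs it, and the DMC reviews clean data on the primary and secondary outcome variables. The section then fixes what can follow: "The outcome of this interim analysis will result in one of three possible recommendations of the DMC to the Sponsor". The three entries are:

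- a halt for lack of prospect of benefit: "Stop the study because of futility"
- no change to the trial: "Continue and finalize the study as planned"
- enlargement of the trial: "Continue the study as planned but increase the sample size to a specified number of patients"

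Under Study population the planned size is given: "Recruitment will continue until 100 patients have been randomized into the 2 groups (active substance and placebo) of 50 patients each". Under Study design the endpoint is given: "Primary outcome for this study will be 30-day mortality". The secondary outcomes are intracranial pressure (ICP) and treatment intensity level (TIL).

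On safety elsewhere, the protocol has the treating physician assess adverse events daily (Adverse events) and allows the code to be broken for a single patient after a serious adverse event (Substance identity). Section 8.2.3 gives the sponsor's expectation: "The risk of harm to participants is estimated to be extremely low".

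**The concern.** A committee with safety in its name reviews unblinded deaths by arm in a population where the protocol assumes 40% control mortality. If the deaths lean against the active arm, none of the three listed recommendations fits. Calling the result futility would misname it, continuing would ignore it, and enlarging the trial would add exposure. A DMC charter that added a safety stop would contradict the protocol's statement that the outcome is one of three, so the gap cannot be closed cleanly outside the protocol.

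The timing adds to the problem. With the look at patient 95, an adverse mortality signal would first be seen by arm when nearly all planned exposure has already taken place. Some participants are enrolled before next of kin has been found, and the protocol's consent section rests this partly on minimal risk. That makes it more important that the committee can act on evidence to the contrary.

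**Working it through.** **1. Is a safety stop available at the interim?** Setting the three entries against the possible states of the data:

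| Interim data | Listed recommendation that fits |
|---|---|
| Little prospect of showing benefit | Stop for futility |
| On track | Continue as planned |
| Promising but underpowered | Continue with a larger sample |
| Excess deaths or serious events in one arm | None listed |

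**2. What data does the committee see?** Primary and secondary outcomes only: 30-day mortality, ICP and TIL. Adverse events (AEs) and serious adverse events (SAEs) are not among the interim inputs.

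**3. How much exposure precedes the look?** Inputs: 95 included (Interim analysis) and 100 planned, 50 per arm (Study population).

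- Fraction enrolled: 95/100 = 95%. Remaining: 100 − 95 = 5.
- With 50 active and 50 placebo packs and 5 unused, the active arm holds between 45 and 50 patients. The expected number is 95 × 0.5 = 47.5.

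**4. When would the data be ready?** Under Study status, recruitment runs from September 2017 to June 2021, about 45 months. Assuming even recruitment:

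- Rate: 100/45 = 2.2 patients per month.
- Included when patient 95 reaches day 30: 95 + 2.2 = about 97.
- Time from patient 95 to patient 100: 5/2.2 = about 2.25 months.

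After follow-up and data cleaning, the look falls at or near the end of planned recruitment.

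**5. Is there another route to a comparison of deaths by arm?**

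- Code breaks are for single patients and do not compare arms.
- The AE definition covers events resulting from participation. The examples listed are rash and hives, and serious anaphylaxis. A death attributed to the brain injury would not necessarily be captured.
- The external monitoring visits, 2 to 4 a year, are not described as an unblinded review.

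**6. Could an earlier look detect harm?** The protocol gives no harm scenario, so active-arm mortality is assumed here. Placebo mortality is the protocol's 40%. As a check on method, Fisher's test on 8/50 against 20/50 gives p = 0.0135, odds ratio 0.289 and 95% interval 0.097 to 0.797. These match the protocol's stated 0.01, 0.29 and 0.10–0.80.

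The table shows the chance that a two-sided Fisher test shows excess deaths on active, by exact enumeration over both binomial counts. The levels are assumptions.

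| Active mortality | 30 pts, p≤0.01 | 60 pts, p≤0.01 | 50 pts, p≤0.05 | 95 pts, p≤0.05 |
|---|---|---|---|---|
| 50% | 1% | 2% | 8% | 14% |
| 60% | 4% | 12% | 24% | 46% |
| 64% | 7% | 19% | 33% | 62% |

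A strict significance threshold at an early look would seldom be crossed. This argues for DMC judgement on the tabulated deaths and SAEs, and against a fixed early boundary.

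**The case against.** **The list governs one analysis.** The protocol limits the outcome of this interim analysis. It does not say that the committee does nothing else, nor does it bar safety advice at other times. A charter or SAP, not shown, may provide for earlier safety review. This stands. A reader might infer that the trial has no safety oversight, or that the committee's safety role goes undelivered, and the protocol does not support that. Physicians assess AEs daily, codes can be broken after an SAE, and AEs and SAEs are handled under the ethics permit and GCP. None of this is a comparison of deaths by arm, however, and none of it changes the closed list.

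**No mechanism of harm is identified.** The protocol reports no known toxicity and rates the risk as extremely low. Aspiration might come to mind as a danger specific to the active arm, but placebo is also egg yolk powder, given in the same way through the same tube. Any such risk from the feed itself would be expected in both arms, so it does not support the point. The point does not need a named mechanism: the low risk is an estimate, and the committee will be looking at deaths by arm in any case.

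**Early looks have little power.** This is correct, as step 6 shows. A reader might infer that looks at fixed early sample sizes with a formal p-value boundary are required. The documents do not require this, and the calculation does not favour it.

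**A committee could use the futility option when it sees harm.** It might, but the protocol does not say so, and the report would then misstate why the trial stopped.

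**Conclusion.** The point holds as a defect in stated text. The interim list is closed at three and has no entry for safety, while one of the three permits more exposure. The interim inputs leave out AEs and SAEs. The only comparison between arms described before the end comes at 95% enrolment, with at most 5 planned patients still to enter, and at about 97 enrolled once patient 95 reaches day 30. That last figure assumes even recruitment over 45 months. A stop at that look has practical protective value mainly if the sample is to be enlarged.

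The missing recommendation and the missing safety inputs rest on the protocol's own words and should be corrected. Whether to add an earlier review is a softer question: the protocol describes none, but an unseen charter could, and the choice of timing is one of design.

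**What to change.** 1. Under Interim analysis, change three recommendations to four and add: *Pause or stop the study for safety (excess mortality or serious adverse events)*.
2. Add AEs and SAEs by arm to the data the DMC reviews at the interim.
3. Reconcile the list with the committee's safety remit, so that the protocol and any charter agree on what the DMC may advise and when.
4. Consider at least one earlier closed-session review of deaths and SAEs by arm, prepared by the unblinded statistician already planned and left to the DMC's judgement. Timing and any threshold are for the sponsor and the DMC to settle.

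The cost is a protocol amendment, matching charter wording and a short additional table. There is no alpha cost: a stop for harm can only remove trials that might otherwise have gone on to claim benefit, so it does not inflate the false-positive rate for benefit.

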**Study enrolment procedures**

- - 1. **Identifying and recruiting candidates for the trial**

When a patient with severe traumatic brain injury is admitted to the Neurointensive Care Unit, the neurosurgeon on call will evaluate the patient, ask for informed consent from next of kin, if available, and use the screening protocol for inclusion.

All patients that are screened will be recorded in the screening log. Reasons for ineligibility and for non-participation of eligible candidates will be recorded in the log.

- - 1. **Consent procedures**

The study coordinator or a person authorized by the study coordinator will come to the bedside of the patient and introduce him/her-self to the relatives. The project will be described in general terms and the relatives of the patient will be informed that the patient is eligible for inclusion in the study. The study coordinator will take the family to a place where they can talk confidentially, and describe every aspect of the project. Time will be given to ask questions, and the family will be asked to repeat back in their own words what has been discussed, to make sure that they understand. The potential advantages and disadvantages of participating in the study will be described, and the care of the patient if included in the study, and if not in the study will be described.

The family will be especially informed that participation in the study is completely voluntary and that if they wish to participate, they are free to quit the study at any time.

Next to kin of the eligible participant will be provided with written information about the study, which also includes complete contact information for the study coordinator and co-investigators. Written approval will be obtained in the presence of a witness.

The Investigator will store the original version of the Subject Information and Consent Form and a copy will be given to the subject´s family. Samples of the English version of the Subject Information and Consent Forms will be enclosed. Afrikaans and Xhosa translations of the approved English version will also be provided and enclosed in the Ethics application.

If next of kin is not found after screening of a patient the patient can be included in the study according to the latest Helsinki Declaration (2013) , paragraphs 28-30 where it is stated that if a patient is incapable of giving consent due to a condition that is a necessary characteristic of the research group (eg severe TBI) , the intervention cannot be delayed, there is likelihood that the intervention will benefit the participant and there are minimal risk with the intervention. If a patient s included without consent from next of kin, consent to remain in the research must be obtained as soon as possible from next of kin.

- - 1. **Randomization procedure**

Patients will be assigned a number between 1 and 100. 50 boxes containing Salovum®^®^ and 50 boxes containing ordinary egg yolk powder will be assigned a number between 1 and 100. The study will be conducted in a double-blind fashion and neither the investigators nor the patients will know who receives Salovum®^®^.

- - 1. **Substance identity**

Salovum®^®^ will be packaged into 5 plastic bags each containing 100g which will be packaged into one bag. 50 bags of Salovum®^®^ will be sealed and marked with a random number between 1 and 100.

Identically looking placebo, ordinary egg yolk powder will be used for placebo group. Placebo will be packed the same way as Salovum®^®^ and 50 packages will be marked with random numbers between 1 and 100.

The key to which boxes that contain active substance will be kept in two sealed envelopes that will be kept locked up until after completion of the study. Individual patients may be unblinded in the case of a serious adverse event. A locked box at the study site, containing 100 sealed envelopes can be accessed in the case of a serious adverse event. The investigator can open the envelope containing the patients´ study number and inside the envelope it is clearly stated if the patient has received Salovum® or placebo.

